(A)*Active MNRB™* will be practiced relaxed, sitting back in a chair no more than 30° from the horizontal, with both feet flat on the floor, hands on thighs with palms facing downward. Participants are further instructed to not talk or make any movements during their treatment session. The BarTek™ respiratory gating device is placed upon the diaphragm—around the abdomen, below the rib cage, and an inch (about two finger widths) above the navel. Participants open the MNRB™ program on the Krüger&Matz Flow 5 Android phone, which is connected wirelessly via Bluetooth to the BarTek™ respiratory gating device, and are guided through a 15 min MNRB™ breathing intervention which guides participants from an average respiration rate of 12 breadths/min to a resonance frequency rate of 6 breadths/min—the most optimal means of increasing cardiac-vagal tone (HRV) via respiration [47]. Out of a full (100%) breathing cycle, participants are instructed to use the stomach to breathe in to full inspiratory capacity for 30% and exhale for 60% by tightening and pulling the stomach back toward the spine. At the end of each inspiration and expiration, participants are instructed to retain their breadth for 5% of the cycle [62]. The participant is instructed to allow the chest to remain immobile throughout the entirety of the session [63, 64]. This is achieved through a feedback system actively engaging the patient to follow an orb that indicates stages of breathing and constantly correcting participants when they practice. While practicing, participants are to engage in a nondirective state of mind [65], where a relaxed focus of attention is established by listening to the inspiration and expiration sound guides of the MNRB™ program. Attention is neither directed toward staying with the respiration sound guides nor directed toward observing the spontaneous flow of thoughts and sensations [65]. Sensations, such as pain, during MNRB™ are accepted without actively directing attention toward them or away from them [7].

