(B)*Sham MNRB™* is practiced relaxed, sitting back in a chair no more than 30° from the horizontal, with both feet flat on the floor, hands on thighs with palms facing upward. Participants are instructed not to talk or make any movements during their treatment session. Participants will be instructed to breathe at the normal respiration rate for an adult (12 breadths/min) [66] by following a respiratory pacer [67] on the Krüger&Matz Flow 5 Android MNRB™ program while counting their breadth [53]. Out of a full (100%) breathing cycle, participants are instructed to breathe normally with a 49% inhale and a 49% exhale without any (i.e., 1%) breath retention at the end of each inspiration and expiration. Participants are instructed to maintain a focused attention on their breath while actively detecting mind wandering [68].

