**Fig. 3 Fig3:**
[figure not shown]
Signal processing pipeline for CameraHRV (Table taken from [80])

This study will use resting HRV recordings of 1 min. Reducing the HRV recording window to a duration of 1 min, in comparison to the standardized 5-min recording, is acceptable when rMSSD is considered as the primary HRV parameter of interest [81]. A 1-min recording of the natural log of rMSSD (lnRMSSD) has also been proven to offer good reliability in comparison to the classical 5-min recording of rMSSD [82]. Furthermore, high-frequency HRV (hfHRV) also shows reasonable agreement between ultrashort-term recording windows (60 s or less) and 5-min periods [82, 83]. Several studies use hfHRV as an index of vagal tone [47] due to its strong correlation with rMSSD [84, 85]. However, unlike hfHRV, rMSSD has been shown to be insusceptible to confounding respiratory effects during the recording window [26, 83]. In addition to the main analysis performed with one ideal variable reflecting vagal tone (RMSSD), it is recommended [47] that researchers perform the same analyses with the other variables depicting vagal tone (hfHRV, SDNN, and pNN50). Date and time of day for every HRV recording will be saved within the CameraHRV program which can be used as a proxy for treatment compliancy for all participants during their 2-week home treatment.

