#### Daily intervention procedure (Fig. 8)

Upon waking or going to sleep, participants are to take a 1-min HRV recording with CameraHRV before and after their assigned 15-min treatment intervention. Participants are instructed to use the same HRV recording procedure as in CVI and CVII: sitting in a relaxed semi-Fowler position no more than 30° from the horizontal, knees at a 90° angle, while breathing normally, with both feet flat on the floor without moving or talking. Due to the fact that circadian rhythms and digestion have an impact upon HRV [107, 108], time of day and time since last meal should be standardized when possible in short-term HRV recordings, especially for designs incorporating repeated recordings over time [26]. Therefore, participants are instructed to take their HRV recordings preferably at the same time every day in the morning and at night before and after their assigned intervention. Furthermore, participants are instructed to keep a normal sleep schedule throughout their 2-week intervention while abstaining from consuming any large meals, caffeinated drinks, nicotine, or alcohol immediately prior to their morning HRV recordings and no less than 2 h before their evening HRV recordings. HRV recordings will be saved locally on the assigned Krüger&Matz Flow 5 phone and labeled with the participant’s assigned Viedoc identification number. Participants are to legibly encircle their NRS after each 1-min HRV recording (four times per day) in their Daily Treatment Journal throughout the 2-week intervention period.

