### Limitations

Within-subject designs are typically recommended over between-subject designs for HRV experiments—unlike between-subject designs, within-subject designs offer optimal experimental control and reduce the impact of external factors such as medication, alcohol, and smoking [102]. However, within-subject designs for HRV research also suffer from many inherent weaknesses (such as the learning effect that can be observed in some experimental tasks [47]. If a between-subject design is chosen with testing occurring on different days, it is recommended that participants take part in the experiment at the same time of the day [107]—a practice which has been implemented in this current study.

As mentioned in previous studies investigating pain and respiration [121, 122], not blinding the experimenters to the intervention can be seen as a limitation. Even though it is typically considered unfeasible to blind the experimenter to the intervention for investigations of this kind, it has been recommended [123] that studies document expectation bias by carefully designing and standardizing the intervention instructions and measuring participants’ expectations about the effectiveness of the to-be-delivered intervention—both of which are exercised in this study. Nonetheless, the difficulty in designing a reliable sham breathing protocol for experimental and clinical trials is quite apparent—trials that implement sham breathing protocols commonly instruct participants to either “breathe normally” [53] or “spontaneously breathe” [124] while “focusing on their breadth” [125]. Unlike a pharmacological intervention, a behavioral therapy is not easily controlled and participants can potentially know which intervention they are receiving [51]. This is especially true for trials employing deep breathing exercises due to the fact that the sham, normal paced breathing, is known to be commonly associated with resting and not with active treatment. Longitudinal research [126] comparing daily variations of time and frequency-based HRV parameters between controlled breathing (i.e., pacer breathing) and spontaneous breathing (i.e., natural breathing) sessions found that significant time-based HRV correlations exist between these two different conditions (especially in regard to rMSSD). This demonstrates that during a longitudinal follow-up, these markers provide the same HRV variations regardless of breathing pattern.

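### In the MNRB comparison, the within-session hfHRV change should not be read as a vagal index, because the post-session reading follows different paced breathing rates in the two arms

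*Protocol article*

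**What the plan says.** - **Pacing.** Under the MNRB heading of the Protocol article, the active program "guides participants from an average respiration rate of 12 breadths/min to a resonance frequency rate of 6 breadths/min", described as "the most optimal means of increasing cardiac-vagal tone (HRV) via respiration". Sham participants are told to "breathe at the normal respiration rate for an adult (12 breadths/min" with the help of a pacer.
- **Readings.** Under Daily intervention procedure, "participants are to take a 1-min HRV recording with CameraHRV before and after their assigned 15-min treatment intervention". The reading is to be taken "while breathing normally, with both feet flat on the floor without moving or talking", by the procedure used at the clinic visits.
- **Analysis.** Under Statistical considerations and sample size calculation, the change from the first to the second data point over the 14 treatment days is calculated for HRV, and differences in these changes between groups are tested. The CVI-to-CVII change is analysed as well.
- **Choice of marker.** The CameraHRV section takes RMSSD as the main variable, partly because "unlike hfHRV, rMSSD has been shown to be insusceptible to confounding respiratory effects during the recording window". It then cites a recommendation to "perform the same analyses with the other variables depicting vagal tone (hfHRV, SDNN, and pNN50". No arm and no time point is excepted.
- **Respiration data.** The BarTek section says that respiratory information is saved within the MNRB program. HRV is recorded in a separate app, CameraHRV, and no respiration record is mentioned for the HRV minute.

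**The concern.** Breathing rate is a main feature that separates active from sham MNRB. If some participants go on breathing slowly during the minute after the session, that carry-over runs along allocation and enters the within-session change as if it were a treatment effect. hfHRV is the exposed marker, because it counts only variability inside a frequency band and slow breathing can move the respiratory component out of that band.

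The article names this weakness and, in the same paragraph, endorses the analysis that has it, in the one comparison where breathing rate is the treatment. A supportive marker could then fall in the active arm, and seem to contradict RMSSD, for a reason unrelated to vagal tone. Without respiration data for that minute, the two explanations could not be separated afterwards.

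**Working it through.** **1. The plan's own figure.** For a standardised difference of 0.9, two-sided 0.05 and power 0.8, the two-sample t-test needs 20.4, so 21 per group, as stated. With 28 per group its power is 0.911, against 0.9 stated. Both figures reproduce, and nothing below changes them.

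**2. Paced rates as frequencies** (f = breaths per minute / 60).
- Active: 6/60 = 0.10 Hz.
- Sham: 12/60 = 0.20 Hz.

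**3. Position relative to the HF band.** The article gives no band limits, so let L be the lower limit (assumption). Breathing below 60 × L breaths/min puts the respiratory peak outside the band. L = 0.11 Hz gives 6.6/min, 0.15 Hz gives 9/min and 0.19 Hz gives 11.4/min. For every L between 0.10 and 0.20 Hz, 6/min is outside and 12/min is inside. The result does not depend on one chosen limit.

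**4. What enters the contrast.** Write each arm's change as post minus pre. The difference between arms is then the true effect plus (carry-over in active − carry-over in sham). The article itself calls 12/min the normal adult rate, so carry-over in sham should be close to none. In the active arm it would lower hfHRV, by an amount that depends on how many participants stay below 60 × L and on how much of their hfHRV is respiratory. The documents give neither.

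**5. Illustrative size.** Suppose there is no true effect, one summary change per participant, and carry-over shifts the active mean by b SD of that change. The rejection rate of the two-sided 5% t-test (non-centrality b × √(n/2)) is:

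| Shift b (SD) | n = 28 per group | n = 21 per group |
|---|---|---|
| 0.1 | 6.6% | 6.2% |
| 0.25 | 15.1% | 12.4% |
| 0.5 | 45.1% | 35.3% |

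The shift would lower hfHRV under active MNRB, so most of these rejections would point to an apparent loss of vagal tone. A real gain of the same size would be cancelled.

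**6. RMSSD and SDNN under the same mechanism.** Model the respiratory oscillation of the RR interval as a sinusoid of amplitude A and frequency f, with mean RR interval T. Then RMSSD = √2 × A × |sin(πfT)| and SDNN = A/√2. Assume that pacing persists in full.
- T = 0.7 s: RMSSD is 0.309A at 6/min and 0.602A at 12/min, ratio 0.51.
- T = 1.0 s: 0.437A and 0.831A, ratio 0.53.
- An amplitude 1.9 to 2.0 times larger at 6/min cancels the difference. A 3-fold amplitude reverses it, since 3 × 0.51 to 0.53 is about 1.5 to 1.6.
- SDNN does not depend on rate at all and moves only if the amplitude moves.

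For these two markers the sign rests on an amplitude that the documents do not give.

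**The case against.** A reader might infer that the reading comes immediately after the session with no rest. The text does not establish this. It says only that the reading comes after the session; the figure of the home procedure is not shown; and the clinic procedure to which it refers includes at least 5 minutes seated beforehand. That part stands: absence of a rest cannot be asserted. It does not settle the matter either. The home text goes on to list posture, ordinary breathing and stillness but not that period, and someone who has just sat through 15 minutes of pacing could regard a seated period as already met.

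Ordinary breathing is required in every arm, so only involuntary carry-over is at issue. That stands too, and it is why the size is unknown.

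A stronger reading would be that the RMSSD and SDNN results are compromised as well. The documents do not support it. RMSSD was chosen with respiratory confounding in mind, and step 6 shows that its shift can go either way or vanish. The Limitations sentence, "these markers provide the same HRV variations regardless of breathing pattern", follows a statement about time-based correlations. It neither defends hfHRV nor claims equal levels. Correlation would not exclude a difference in level, but that is no evidence of bias in RMSSD. Nor does describing slow breathing as the route to higher HRV conflict with taking a later reading under ordinary breathing.

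Finally, the extra markers are supplementary and worded as a recommendation, and an analysis plan might restrict them. That limits the weight of the point. It does not remove the tension inside the CameraHRV section, which endorses the hfHRV analysis without exception.

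**Conclusion.** The point holds for one supportive marker in one comparison: the within-session hfHRV change in active versus sham MNRB. The two arms leave their sessions at 0.10 and 0.20 Hz. The text neither fixes a breathing washout nor states a respiration record for the reading, and it treats hfHRV itself as open to this confounding.

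The size cannot be derived from the documents. The shifts of 0.1 to 0.5 SD are assumptions, giving false rejection rates of 6.6% to 45.1% with 28 per group. The direction rests on a lower HF limit between 0.10 and 0.20 Hz and on some participants continuing to breathe slowly. The RMSSD and SDNN figures are illustrations and support no claim of bias.

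Not affected by this mechanism are the tVNS contrast, where both versions use ordinary breathing; the CVI-to-CVII change, which is measured at clinic visits after acclimatisation; and the sample size.

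**What to change.** State in the analysis section that, for the active-versus-sham MNRB contrast, the within-session (pre/post) hfHRV change is not interpreted as an index of vagal tone. Confine hfHRV there to the CVI and CVII resting readings, and keep RMSSD as the main within-session variable.

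The cost is analysis wording and the loss of one supportive marker for that contrast. It needs no new data and can be settled before unblinding.

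Three more ambitious changes are not advised:
- **Adding a rest before the home reading now.** Recruitment is under way, so this would mix two measurement procedures.
- **Dropping readings taken below a set breathing rate.** This selects on a variable that the treatment itself shifts. If those readings then counted as missing, the plan's rule of filling a post-session value with the pre-session one would force a change of zero.
- **Deleting the Limitations sentence.** This is editorial and would not alter the analysis.

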**Fig. 8 Fig8:**
[figure not shown]
Daily home intervention procedure

## Discussion

CWP, including FM, affects one in ten individuals within the general population [109] and has the highest prevalence in Norway (12–30%) [110] where it is a leading cause of long-term sick leave and disability [111]. Due to an overall lack of efficacy in both mainstream [112] and alternative [6] treatments, it is necessary to develop new avenues for treatment.

### Strengths

A recent systematic review [8] called for future research to identify the autonomic/cardiovascular mediators that link respiration and pain; identify the physiological (i.e., respiratory) mechanisms needed to reduce pain; identify the central mechanisms responsible for producing respiratory hypoalgesia; and identify the psychological (i.e., behavioral) mechanisms needed to reduce pain. This clinical trial will answer that call by investigating whether the autonomic mediator that links respiration and FM is HRV; the physiological mechanism needed to reduce pain in those with FM is a 30-5-60-5 diaphragmatic breathing (i.e., resonance frequency breathing) technique; the central mechanism responsible for producing respiratory hypoalgesia is vagus nerve stimulation (either through respiratory or electrical means); and the cognitive and affective psychological mechanisms needed to reduce pain in those with FM is nondirective attention and motivation.

Meditative-based breathing techniques commonly investigated in clinical trials are often poorly described [113–115] and do not account for the relative frequency of diaphragmatic movement with precision, nor does it account for effects of expectation and attention on pain outcomes [8]. MNRB™ will be delivered to participants with specific instructions in regard to breathing frequency, volume, and breathing mechanics. Monitoring the participants’ breathing with the BarTek™ respiratory belt will show how well patients have complied with these instructions and help identify pain-related compensatory changes in breathing depth and frequency. Participant treatment expectation will be accounted for through the Credibility/Expectancy Questionnaire (CEQ) prior to the start of their active or sham MNRB™ intervention. And attention/distraction will be controlled for by giving the sham-control group a sham MNRB™ technique of counting the breath.

Vagus nerve innervation as a means of pain treatment has been traditionally administered through invasive procedures, known as invasive vagus nerve stimulation (iVNS), which has typically involved the surgical implantation of electrodes around the cervical vagus nerve [116]. iVNS is often accompanied with a high risk for adverse events (e.g., voice alteration, paresthesia, cough, headache, dyspnea, pharyngitis, and pain at the site of stimulation) [72]. This study will deliver transcutaneous VNS (tVNS) as a safe and effective alternative which allows the user to directly modulate stimulation intensity, pulse duration, and frequency accordingly [117]. Both means of vagal stimulation (MNRB™ and tVNS) are easy to use, portable, and safe and are able to be tailored to a patient’s stimulation or respiratory threshold. These factors increase the probability for patient compliancy and overall satisfaction with the treatment interventions.

Treatment compliance is heavily dependent upon treatment duration. Most researchers have traditionally assumed that meditation practice has its effects in a cumulative way through long-term practice. However, current research [118] shows that short-term influences of meditation practice have a more promising effect upon clinical outcomes. Continual meditation practice may not be necessary for maintaining beneficial psychophysiological effects [119]. This study shares this notion by employing a mind-body intervention which lasts only 2 weeks (as compared to the traditional 8-week mindfulness program) and practiced for only 30 min in total each day. Shortening the typical daily practice duration of mind-body interventions [68] as well as practicing in a natural setting [120] increases participant compliancy and satisfaction.

### Limitations

Within-subject designs are typically recommended over between-subject designs for HRV experiments—unlike between-subject designs, within-subject designs offer optimal experimental control and reduce the impact of external factors such as medication, alcohol, and smoking [102]. However, within-subject designs for HRV research also suffer from many inherent weaknesses (such as the learning effect that can be observed in some experimental tasks [47]. If a between-subject design is chosen with testing occurring on different days, it is recommended that participants take part in the experiment at the same time of the day [107]—a practice which has been implemented in this current study.

As mentioned in previous studies investigating pain and respiration [121, 122], not blinding the experimenters to the intervention can be seen as a limitation. Even though it is typically considered unfeasible to blind the experimenter to the intervention for investigations of this kind, it has been recommended [123] that studies document expectation bias by carefully designing and standardizing the intervention instructions and measuring participants’ expectations about the effectiveness of the to-be-delivered intervention—both of which are exercised in this study. Nonetheless, the difficulty in designing a reliable sham breathing protocol for experimental and clinical trials is quite apparent—trials that implement sham breathing protocols commonly instruct participants to either “breathe normally” [53] or “spontaneously breathe” [124] while “focusing on their breadth” [125]. Unlike a pharmacological intervention, a behavioral therapy is not easily controlled and participants can potentially know which intervention they are receiving [51]. This is especially true for trials employing deep breathing exercises due to the fact that the sham, normal paced breathing, is known to be commonly associated with resting and not with active treatment. Longitudinal research [126] comparing daily variations of time and frequency-based HRV parameters between controlled breathing (i.e., pacer breathing) and spontaneous breathing (i.e., natural breathing) sessions found that significant time-based HRV correlations exist between these two different conditions (especially in regard to rMSSD). This demonstrates that during a longitudinal follow-up, these markers provide the same HRV variations regardless of breathing pattern.

Even though a number of studies using high-intensity tVNS have not found any major side effects, as mentioned before, tVNS can still be accompanied by slight pain, burning, tingling, or itching sensations near the sight of the electrodes [72]. There is also no scientific consensus regarding the frequency and strength of tVNS stimulation for pain treatment [9] nor is there a clear understanding of how a constant pulse frequency mirrors endogenous vagal nerve activity—the vagus nerve most likely does not communicate/activate in regimented 30-s consecutive intervals as most of the tVNS devices do [127].

